### Recruitment

Recruitment takes place in two steps: First: primary care practices are recruited; and second: the participating GPs invite their patients to participate in the study. Two study centers, Hamburg and Würzburg, recruit general practices in four recruitment regions: Hamburg, Kiel, Lübeck (northern Germany) and Würzburg (southern Germany). The recruitment of the primary care practices began in April 2012 and will last until January 2014. All primary care practices in Hamburg, Kiel, Lübeck and Würzburg and within a 50 km radius of these cities, (to include urban and rural areas), receive a written invitation to participate in the study. If not responding to the invitation, study staff contacts each general practitioner by phone.

In a second step, participating GPs apply the following search criteria to identify eligible patients from the electronic records: age 18 and above, last consultation within the last six months, and any diagnosis of heart failure (ICD-Codes beginning with I50, I11.0, I13.0, I13.2) documented within the last 5 years. Out of all patients, who meet the mentioned criteria those who passed away since the last consultation or suffer from dementia are excluded (for a complete list of all inclusion and exclusion criteria see Table 1).

**Table 1 T1:** Inclusion and exclusion criteria

	**Observation group 1 (P+/+)**	**Observation group 2 P(+/−)**	**Observation group 3 P(−/−)**

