**Figure 1 F1:**
[figure not shown]
Baseline and follow-up assessment.

The 75% randomly selected patients without depression and/or anxiety provides a higher number of patients in the observation group 3 (P−/−) than the power calculation suggests (see section *Sample size calculation*). The higher number is chosen for quality assurance. A group of patients without depression and anxiety which is too small would reveal the focus on depression and anxiety in this study. Therefore the proportion of patients with depression and/or anxiety and without depression/anxiety will be 1:3 in each interview.

Symptoms of anxiety and depression are addressed within a full list of somatic comorbidities, introduced by the somatic conditions of the Charlson Comorbidity Index [46] and followed by a question concerning any further comorbidity, which has not been addressed in the list before. The focus on depression and anxiety within this study is not revealed to the GPs. During the interview the GPs have full access to all patient data within their electronic records. The recognition of depression and/or anxiety is operationalized as the GP’s judgement in the telephone interview as to whether or not the patient displays symptoms of depression and/or anxiety. If the GP states that the patient displays symptoms, the GP is asked if he or she judges this as a clinical diagnosis or if he or she considers the symptoms not severe enough for a diagnosis.

In a next step, patient information from the questionnaire and GP judgment regarding depression and anxiety are matched and the patients are allocated to one of the following groups:

● Observation group 1 (P +/+): All patients with depression and/or anxiety whose depression and/or anxiety has been recognized by the GP

● Observation group 2 (P +/−): All patients with depression and/or anxiety whose depression and/or anxiety has not been recognized by the GP

● Observation group 3: P (−/−) Sample of patients without depression and anxiety who were randomly selected for telephone interview. In the interview the GPs did not diagnosed any depression or anxiety.

Patients without depression and anxiety whose GP nevertheless diagnosed depression or anxiety P(−/+) will be considered separately.

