### Sample size calculation

Given a prevalence of psychosocial risk factors (depression, anxiety or both) in HF patients from general practices of 20% [6] and a recognition rate of 75% [20], we aim for a sample that provides us a minimum power of 80% to detect a minimum difference of at least any 5 points on the EQ-5D visual analogue scale (EQ-VAS) [42] with α = 0.05. Therefore, a sample of 672 participants with depression and/or anxiety is needed, of whom 504 have depression and/or anxiety recognized by their GP (P+/+) and 168 with depression and/or anxiety not recognized by their GP (P+/−).

Given an estimated participation rate of 40%, a return rate of the baseline questionnaire of 90% and a loss to follow-up rate of 15% a total of 10,973 patients with heart failure are needed to be invited into the study by their GP (see Figure 2).

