### Data analysis

The prevalence of comorbidities in patients with HF and difficulties in the treatment of patients with HF will be analyzed by descriptive statistics. The prevalence of recognition/non-recognition of psychosocial risk factors in primary care HF patients and its impact on the study endpoints will be analysed. In a first step we will compare quality of life, hospitalisation and mortality after a 1-year follow-up period between HF patients with depression/anxiety (P+/+ and P+/−) and those without (P−/−).

In the second step we will compare quality of life, hospitalisation and mortality after a 1-year follow-up period between HF patients with depression and/or anxiety recognized by their GP (P+/+) and those with depression and/or anxiety not recognized (P+/−). We will perform multivariate regression models taking the confounding effects (e.g. comorbidity, sociodemographics, type of treatment for depression/anxiety and heart failure severity) into account.

In a third step we will compare several types of treatment for psychosocial risk factors and their potential effects on quality of life, hospitalisation and mortality after a 1-year follow-up period.

We will compare the information concerning the treatment of psychosocial risk factors gathered from patients with that gathered from GPs to evaluate potential differences (e.g. due to treatment initiated by other healthcare providers than the GP). We will re-run the analyses of the third step for information gathered from patients and for information gathered from GPs separately.

For binary outcomes (hospitalization, survival after 1 year), chi-squared tests will be used. For continuous outcomes (quality of life, survival time), t-tests or non-parametric rank tests will be used. Multivariate linear regression analyses will be performed for the total number of hospitalized days, Cox regression and Kaplan-Meier curves for time to hospitalization survival time. Multivariate linear regression will be used for quality of life.

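### Patients are nested in GP practices and recognition is the GP's own judgement, yet neither the sample size nor the analysis states any allowance for clustering

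*Protocol article*

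**What the plan says.** All references are to the Protocol article.

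- *Recruitment*: sampling has two stages. Practices are enrolled, and then "the participating GPs invite their patients to participate in the study".
- *Recognition of depression and anxiety* (Methods/Design): recognition is "operationalized as the GP’s judgement in the telephone interview", made patient by patient. The comparison group without depression or anxiety is drawn as 75% of such patients within each practice.
- *Sample size calculation*: the target is "a minimum power of 80" per cent to "detect a minimum difference of at least any 5 points on the EQ-5D visual analogue scale (EQ-VAS) [42] with α = 0.05". The section concludes that "a sample of 672 participants with depression and/or anxiety is needed", split into 504 recognised (P+/+) and 168 not recognised (P+/−). It gives no SD, number of practices, patients per practice, ICC or design effect.
- *Data analysis*: "For binary outcomes (hospitalization, survival after 1 year), chi-squared tests will be used", and t-tests or rank tests for continuous outcomes. Linear regression is named for quality of life and hospital days, and Cox regression for times to event. The confounders are given as examples. No practice or GP effect, mixed model, GEE, frailty term or cluster-robust error is mentioned.

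**The concern.** Patients of one practice share a GP, a catchment area and a style of care, so outcomes such as hospital admission and quality of life may be correlated within practice. The exposure may be correlated too, because one GP judges several patients and GPs differ in how readily they see depression or anxiety. When both cluster, a test that treats patients as independent understates the standard error of the P+/+ versus P+/− contrast. A sample size with no design effect then overstates the power.

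The recognition rate is itself a stated research question and is meant to inform GPs and health planners. For a single proportion, clustering of recognition alone is enough to make an independence-based interval too narrow.

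A separate issue is confounding. A GP who recognises depression more often may also manage heart failure differently. The adjustment variables listed as examples are comorbidity, sociodemographics, type of treatment and heart failure severity. None of them separates such differences between practices from the effect of recognition.

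**Working it through.** **Inputs from the article.** Difference 5 EQ-VAS points; α 0.05 (two-sided assumed, as sidedness is not stated); power 80%; prevalence 20%; recognition 75%, hence 3:1 groups; 504 and 168 analysed; participation 40%, questionnaire return 90%, loss to follow-up 15%.

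**Inputs assumed, because the article gives none.** SD 20; m = 3.5 patients with depression/anxiety per practice; outcome ICC 0.02–0.10; recognition ICC 0.1–0.5 for the contrast and 0.1–0.3 for the recognition rate.

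**1. Reproduce the plan's figure.** Standard error for independent patients: 20 × √(1/504 + 1/168) = 1.782. Then 5/1.782 = 2.806 and power = Φ(2.806 − 1.960) = 80.1%. The same formula returns exactly 168 + 504 = 672. Solving back from 672 gives an SD of 20.03.

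The recruitment chain also closes without a clustering factor: 10,973 × 0.40 × 0.90 = 3,950; × 0.20 = 790; × 0.85 = 671.5, that is 672.

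This is a fit, not proof. An SD of 20.03/√1.2 = 18.3 with a design effect of 1.2, or 20.03/√1.1 = 19.1 with 1.1, would also give 672.

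**2. P+/+ versus P+/−.** Recognition varies between patients of one practice, so the design effect (DE) is about 1 + (m − 1) × outcome ICC × recognition ICC, and power = Φ(2.806/√DE − 1.960).

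| m | Outcome ICC | Recognition ICC | DE | Power |
|---|---|---|---|---|
| 3.5 | 0.02 | 0.1 | 1.005 | 79.9% |
| 3.5 | 0.05 | 0.3 | 1.0375 | 78.7% |
| 3.5 | 0.10 | 0.5 | 1.125 | 75.4% |
| 10 | 0.05 | 0.3 | 1.135 | 75.0% |
| 20 | 0.10 | 0.3 | 1.57 | 61.0% |

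These powers apply to the simple difference tested with a correct standard error.

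**3. Type I error of the t-test as named.** Simulation with 672 patients, SD 20 and 4,000 runs per setting:

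- Recognition not clustered: 4.4% to 5.5%, even with outcome ICC 0.10.
- Recognition ICC 0.3: 5.9% (m = 7, outcome ICC 0.05), 8.1% (m = 7, 0.10) and 9.9% (m = 14, 0.10).

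The uncorrected t-test still rejected in 76% to 81% of runs at a true 5-point difference. If it is used as named, the cost therefore appears mainly as false positives. If the standard error is corrected, it appears as lost power.

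**4. Recognition rate.** With 790 patients and 75% recognised, the independent 95% half-width is 1.96 × √(0.75 × 0.25/790) = 3.0 points. Here the full DE applies: 1 + 2.5 × 0.1 = 1.25 and 1 + 2.5 × 0.3 = 1.75. The half-widths become 3.0 × √1.25 = 3.4 and 3.0 × √1.75 = 4.0 points.

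**The case against.** The strongest reply is that this is a journal article, and random effects or robust errors are the kind of detail left to a fuller plan. For the regressions that stands. Linear and Cox regression are named without a variance estimator, so clustering is unaddressed rather than excluded. A reader might infer that every listed method treats patients as independent; the text supports this only for the chi-squared, t and rank tests. The reply does not cover those tests or the sample size, which the article sets out explicitly.

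A reader might also infer that the stated 80% power is false. The article does not support that: with the SD unstated, a smaller SD and an unreported design effect fit 672 equally well.

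Nor does the design effect of a cluster-randomised trial apply to the main contrast. Recognition varies within practice, so the inflation depends on the product of two ICCs and may be negligible. Widening the recognition interval by up to one point would not change a conclusion about a rate near 75%, and *Data analysis* names no interval method for that rate. The article also describes its results as helping to generate hypotheses.

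These points limit the size and the severity. They do not supply the missing allowance.

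**Conclusion.** The point holds as an omission with a bounded but unknown effect. The design is clustered, the exposure is set by the GP, no allowance is stated, and the unadjusted tests named assume independence. Their standard errors are too small whenever both recognition and outcome cluster. A recognition-rate interval computed as for independent patients is too narrow whenever recognition clusters.

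Under the assumptions above, with small clusters, the power for the main contrast lies between essentially the stated 80% and about 75%. It falls further only with larger clusters and appreciable values of both ICCs. The recognition interval widens by about 0.4 to 1.0 point on each side. All of this rests on an assumed SD, cluster size and ICCs, and the article gives nothing to narrow the range. It should be fixed before analysis; it does not invalidate the study.

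**What to change.** In *Data analysis*:

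- Fit the group comparisons with practice as the cluster, or GP where a practice has several (Table 2 records the number of GPs and the practice type). Use mixed models or GEE with robust errors for quality of life and binary outcomes, and shared frailty or robust variance for Cox regression.
- Use cluster-robust intervals for prevalence and recognition rates.
- If differences in care between practices are to be separated from recognition, add practice-mean recognition or practice fixed effects. A random intercept or GEE alone does not generally remove that confounding.

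In *Sample size calculation*, state the assumed SD, cluster size and ICCs, and give the power as conditional on them, preferably over a range.

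The cost is wording and a slightly less favourable power statement; no extra patients are needed. Practice membership is already known, since the 75% sample is drawn within practice. A coded practice and GP identifier should be kept in the analysis file before the allocation key is deleted under *Data protection*.

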### Study endpoints

The primary outcome of this longitudinal study is the quality of life after 12-months of follow-up. The secondary outcome is the prognosis of heart failure in terms of hospital admissions and mortality risk within the 12-month follow-up period. Group comparisons will contrast patients with depression and/or anxiety recognized by the GP (observation group 1: P(+/+)), patients with depression and/or anxiety not recognized by the GP (observation group 2: P(+/−)) and patients without depression and/or anxiety whose GPs did not diagnose any depression or anxiety (observation group 3: P(−/−)). For further information see Table 1.

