**GP: Information from medical records (provided by phone)**	
Survival	Mortality within the last 12 month/Date of death/Course of death
Hospital Admission	Number of Hospital Admissions/Date of Admission/Length of stay/Admission diagnosis/Emergency vs. pre-scheduled hospitalization/

Since diagnosis of heart failure will be obtained from the electronic patient records, we will double-check that the heart failure diagnosis is correct at the beginning of the telephone interview with the GP. After validating the diagnosis, the GP is asked to specify the severity level of heart failure according to New York Heart Association (NYHA) functional class. For all further information collected see Table 2.

At the 12-month follow-up assessment the patient receives a second self-administered questionnaire by mail, while data in the general practice will be extracted from the medical records of the practice and are provided by either the GP or practice staff over the phone. For further details regarding the contents of the data collection please refer to Table 2.

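### Survival time is listed for t-tests or rank tests although it is censored at 12 months, which conflicts with the Cox and Kaplan-Meier analyses planned in the same paragraph

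*Protocol article*

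**What the plan says.** Under Study endpoints, the protocol article defines the secondary outcome: "The secondary outcome is the prognosis of heart failure in terms of hospital admissions and mortality risk within the 12-month follow-up period". Table 2 has the practice report, at follow-up, "Mortality within the last 12 month/Date of death/Course of death".

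The last paragraph of Data analysis then gives mortality three treatments:

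- As a binary outcome: "For binary outcomes (hospitalization, survival after 1 year), chi-squared tests will be used".
- As a continuous outcome, in one class with quality of life: "For continuous outcomes (quality of life, survival time), t-tests or non-parametric rank tests will be used".
- As a time to event: "Cox regression and Kaplan-Meier curves for time to hospitalization survival time". A conjunction seems to be missing, but the natural reading covers both time to hospitalisation and survival time.

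The paragraph mentions neither censoring nor the log-rank test, and does not say which of the survival-time analyses governs. For hospital use it adds: "Multivariate linear regression analyses will be performed for the total number of hospitalized days".

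**The concern.** Quality of life at 12 months is a measured value for everyone who returns the questionnaire. Survival time is not. For a patient alive at 12 months the plan knows only that it exceeds 12 months, and for a patient lost earlier only that it exceeds the time of loss.

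A t-test has no place for that information. If survivors are dropped, it compares how early the deaths occurred and ignores how many there were. If censored times are entered as if they were deaths, differences in follow-up count as differences in survival. An ordinary rank test has the same weakness as soon as anyone is lost before 12 months.

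At stake is the unadjusted comparison of mortality, for example between recognised and unrecognised depression or anxiety. It could miss a real difference, or report one produced by unequal follow-up, and it could disagree with the Cox analysis of the same data with no stated rule for choosing between them.

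**Working it through.** **The plan's own figure.** The article gives no sample size for survival; its calculation asks for a "minimum power of 80% to detect a minimum difference of at least any 5 points" on the EQ-VAS "with α = 0.05". With an assumed SD of 20 (none is stated), a two-sided test and 3:1 allocation, the smaller group needs (1.96 + 0.8416)² × 20² × (1 + 1/3) / 5² = 167.4, so 168, and the total is 4 × 168 = 672. The recruitment chain agrees: 10,973 × 0.40 × 0.90 = 3,950; × 0.20 = 790; × 0.85 = 671.5. The 672 therefore rests on EQ-VAS alone.

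**Share censored.** With 12-month mortality m, a share 1 − m is still alive at 12 months. The article gives no m. For assumed values of 5%, 10%, 20% and 30% the share is 95%, 90%, 80% and 70%.

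**Deaths-only reading.** With constant hazard λ = −ln(1 − m)/12 per month, mean time to death among those who die is 1/λ − 12(1 − m)/m.

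- m = 5%: 233.95 − 228 = 5.95 months.
- m = 10%: 113.89 − 108 = 5.89 months.

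The difference is about 0.054 months, under 2 days, although mortality has doubled. In simulation with hazard ratio 2, a rank test among the dead rejected in 4.5% to 7.5% of runs, close to its nominal 5%.

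**Reading that treats observed time as survival time.** Simulation with 504 versus 168 patients and exponential death and loss times, all cut at 12 months, tested two-sided at 5%. There were 2,000 runs per scenario with no hazard difference and 1,000 with hazard ratio 2. The t-test used was the unequal-variance version. Mortality (in the larger group where hazards differ) and loss rates are assumptions. The unequal loss averages 15%: (504 × 0.12 + 168 × 0.24)/672 = 100.8/672.

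| Scenario | Test | m = 5% | m = 10% | m = 20% |
|---|---|---|---|---|
| Hazard ratio 2, loss 15% in both (power) | t-test | 14% | 36% | 79% |
| | plain rank | 20% | 50% | 89% |
| | log-rank | 56% | 83% | 97% |
| No difference, loss 12% vs 24% (false positives) | t-test | 77% | 66% | 52% |
| | plain rank | 89% | 80% | 65% |
| | log-rank | 5.5% | 5.1% | 4.7% |
| Hazard ratio 2, no loss (power) | t-test | 33% | 66% | 95% |
| | plain rank | 58% | 85% | 98% |
| | log-rank | 58% | 85% | 98% |

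With no hazard difference and equal 15% loss, all three tests stayed between about 5% and 6%. Equal loss therefore costs power; unequal loss produces false positives. The 504 and 168 are already net of 15% loss in the plan's chain, so applying loss to them again slightly understates the numbers at risk, for all three tests alike.

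**The case against.** The strongest reply is that the paragraph already contains the right analyses. Chi-squared tests on 1-year survival and Cox regression address mortality risk, which is how the secondary outcome is defined. This stands. A reader might infer that the mortality analysis as a whole is invalid or would miss a doubling of mortality; the document does not support that.

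Second, a rank test can be valid. If everyone is followed to 12 months or death, survivors tie at 12 months and the plain rank test matches log-rank, as the last block of the table shows. Log-rank is itself a rank test, so the wording could loosely include it. This stands in part. The same phrase also serves quality of life, where an ordinary rank test is meant, and the t-test cannot be read as a censored-data method. With complete follow-up, a t-test on time capped at 12 months would compare mean time alive within the year. It still has clearly less power at the lower mortality rates.

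Third, the 15% loss belongs to the EQ-VAS calculation, which depends on a mailed questionnaire, whereas deaths come from practice records. This stands: loss of vital status may be well below 15%, and the biases shrink with it.

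A reader might also infer that linear regression for total hospital days is an error because most values are zero and the standard errors must be wrong. The document gives no admission rate or distribution of days. With an assumed 20% to 60% of patients admitted and skewed stays, simulated type I error of linear regression without covariates at 504 versus 168 was 4.5% to 5.3%. It reached 10% in a constructed case with equal means but different spread (40% × 10 days and 20% × 20 days, both 4 days), where an unequal-variance test gave 5.9%. A difference in mean days is a legitimate target, and preferring a count or two-part model is a modelling choice.

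**Conclusion.** The point holds in a limited form. Naming a t-test for survival time censored at 12 months is a wrong method stated in the document, and an ordinary rank test is safe only with complete follow-up. The fault lies in one unadjusted comparison of a secondary outcome, and it leaves that outcome with two incompatible treatments in one paragraph.

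Its practical size depends on mortality and on loss of vital status, neither of which the article gives. Under the assumed rates it ranges from a modest loss of power (79% against 97% at 20% mortality with equal loss) to a false-positive rate of 52% to 77% for the t-test if loss is 12% versus 24%. These figures illustrate the mechanism and do not forecast this study's results. The primary outcome, the sample size of 672 and the Cox analysis are unaffected.

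**What to change.** Delete survival time from the sentence on t-tests and rank tests. State that survival time is compared by the log-rank test with the planned Kaplan-Meier curves, and by Cox regression for the adjusted comparison, with patients censored at the date last known alive or at 12 months, whichever comes first. Repair the Cox and Kaplan-Meier sentence so that time to hospitalisation and survival time are clearly two outcomes. This is a change of wording. Date of death is already collected; the date last known alive should be recorded in the same practice call for patients not reported dead.

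An optional refinement, not the correction of an error: keep linear regression for total hospital days, use robust or bootstrap standard errors, and add an analysis of hospital days per time alive under observation, so that early death is not read as low hospital use. The cost is one further analysis on data already planned.

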**12-MONTH FOLLOW-UP**	
**Patients: Self-administered questionnaire (by mail)**	
*All measures according to baseline; additional data:*	
Hospital admission within the last 12 month	Number of Hospital Admissions/Date of admission/Length of stay/Admission diagnosis/Emergency vs. pre-scheduled hospitalization
Change of GP	Did you change your GP within the last 12 month? If yes: How many months ago did you change your GP?

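### Baseline quality of life and baseline depression/anxiety severity are not named as covariates for the recognised versus unrecognised comparison, although both are collected

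*Protocol article*

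**What the plan says.** All references are to the protocol article.

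- **Outcome.** Study endpoints makes quality of life after 12 months the primary outcome.
- **Model.** Data analysis says: "Multivariate linear regression will be used for quality of life". For step 2 (P+/+ versus P+/−) it promises regression "taking the confounding effects (e.g. comorbidity, sociodemographics, type of treatment for depression/anxiety and heart failure severity) into account". The same section also lists t-tests or rank tests for quality of life and does not say which analysis is the main result. Step 3 compares types of treatment and gives no adjustment set of its own.
- **Data held.** Table 2 lists the EQ-5D-5L, PHQ-9, GAD-7, HADS and PROMIS scales in the baseline patient questionnaire. At 12 months it repeats them: "All measures according to baseline; additional data".
- **Exposure.** Under Methods/Design, Recognition of depression and anxiety defines recognition as the GP's judgement, at the baseline interview, of whether the patient shows symptoms. A GP who says yes is then asked whether the symptoms amount to a diagnosis or are too mild for one.
- **Target.** Sample size calculation aims at 80% power for "at least any 5 points on the EQ-5D visual analogue scale (EQ-VAS"), "of whom 504 have depression and/or anxiety recognized by their GP (P+/+) and 168 with depression and/or anxiety not recognized".

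**The concern.** Recognition is not randomised, so the step 2 contrast is only as good as its covariates. Patients with more severe symptoms are plausibly easier for a GP to recognise and more likely to be treated. They are also plausibly worse off in quality of life, both at entry and a year later. If so, P+/+ starts lower than P+/−, and a comparison of 12-month values carries that difference forward as though it belonged to recognition. The protocol itself expects non-recognition to be non-random, since its research questions ask which factors are associated with it.

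The printed examples make this sharper. They include heart failure severity but not the severity of the depression or anxiety. They also include type of depression/anxiety treatment, which can follow from recognition. An analyst who used only the printed examples would adjust for a possible consequence of recognition and not for its likely cause. Step 3 faces the same problem as confounding by indication, and Expected implications for practice says its results will be given to GPs as a first orientation on which therapies might help.

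Baseline quality of life is also likely to be among the best predictors of 12-month quality of life, so leaving it out gives up precision.

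**Working it through.** **Inputs from the document.** Difference 5 points; α = 0.05 (sidedness not stated, two-sided used); power 80%; groups of 504 and 168.

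**Inputs not in the document.** The EQ-VAS SD, the correlation r between a baseline score and 12-month EQ-VAS, and the standardised baseline difference d between the groups. These are assumed, with ranges shown.

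**1. Reproduce the plan's figure.** The factor √(1/168 + 1/504) is 0.08909. The SD implied by 80% power is 5 / [(1.960 + 0.842) × 0.08909] = 20.03, so SD = 20 is used.

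- Standard error = 20 × 0.08909 = 1.782.
- Power = Φ(5/1.782 − 1.960) = Φ(0.846) = 80.1%.
- A one-sided test would need only 132 in the smaller group, so two-sided is what matches.

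The stated 672 is therefore an unadjusted two-group comparison with SD 20. At the same group sizes, an SD of 15 would give 96.3% power and an SD of 25 would give 61.2%.

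**2. Possible shift in the unadjusted difference.** Shift = SD × d × r. With no true effect, the chance of a significant result in the direction of the shift is Φ(shift/1.782 − 1.960).

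| d | r | Shift (points) | False rejection |
|---|---|---|---|
| 0.2 | 0.3 | 1.2 | 10% |
| 0.2 | 0.5 | 2.0 | 20% |
| 0.3 | 0.3 | 1.8 | 17% |
| 0.3 | 0.5 | 3.0 | 39% |
| 0.5 | 0.3 | 3.0 | 39% |
| 0.5 | 0.5 | 5.0 | 80% |

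The shift scales with the SD. The range 1.2 to 5.0 becomes 0.9 to 3.75 at SD 15 (15 × 0.06 and 15 × 0.25) and 1.5 to 6.25 at SD 25.

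**3. Precision from adjustment.** Residual SD = 20 × √(1 − r²), at 504 versus 168.

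| r | Residual SD | Power for 5 points | Detectable difference at 80% power |
|---|---|---|---|
| none | 20.0 | 80.1% | 5.0 |
| 0.3 | 19.1 | 83.7% | 4.8 |
| 0.5 | 17.3 | 90.0% | 4.3 |
| 0.7 | 14.3 | 97.6% | 3.6 |

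**4. Make steps 2 and 3 consistent.** Step 2 assumes imbalance, and imbalance costs some precision. The variance is inflated by about 1 + d² × 0.25 × 0.75, which is 1.0075 at d = 0.2 and 1.047 at d = 0.5. Power is then 83.4% to 82.0% at r = 0.3 and 89.8% to 88.6% at r = 0.5. Most of the gain remains at r = 0.5; at r = 0.3 it was small to begin with.

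**The case against.** The best defence is that the covariate list begins with e.g., so nothing is ruled out. The document is a condensed article, and a full covariate list normally sits in an analysis plan, which is not shown. This stands: a reader might infer that the plan leaves these covariates out, and the text does not support that. What remains is that the authors chose which examples to print, and the two covariates closest to exposure and outcome are not among them.

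A reader might also infer that the contrast is confounded and that recognition will look harmful. No figure in the article shows that recognised patients are worse at entry. All P+ patients have met the same case-finding algorithm, and the threshold for recognition is low. The direction is plausible, not documented. The shifts above also apply to the unadjusted difference. The adjustment already promised for comorbidity and heart failure severity would remove an unknown part of them.

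A third tempting reading is that the study is underpowered without these covariates. It is not: on the inferred SD, the planned 80% is met unadjusted.

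Nor does the text force the reading that step 3 is unadjusted. The sentence on linear regression for quality of life is not limited to step 2.

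The remaining objection is substantive. Recognition exists before the baseline questionnaire, and treatment may already have been started, so baseline symptoms and EQ-VAS may partly reflect it. Conditioning on them can remove some of the association of interest. This stands, and it governs how the adjusted result should be read.

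**Conclusion.** The point holds as a gap in what the article fixes, not as an error in it. Baseline depression/anxiety severity and baseline quality of life are collected, bear directly on the recognition contrast, and are not named for its analysis. Unadjusted tests are listed with no statement that they are secondary.

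The possible distortion of the unadjusted difference is about 1 to 5 EQ-VAS points against a 5-point target. This rests on an SD of 20 inferred from the sample size, an imbalance of 0.2 to 0.5 SD and a correlation of 0.3 to 0.5. The forgone gain in power is about 10 percentage points at r = 0.5, and less at r = 0.3. None of the SD, correlation or imbalance can be taken from the document, so these figures show the order of magnitude and do not estimate the bias. If an unseen analysis plan already names these covariates, one confirming sentence closes the point.

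**What to change.** - In the step 2 and step 3 quality-of-life models, name as covariates the continuous baseline PHQ-9 and GAD-7 scores (or HADS) and the baseline value of the quality-of-life score being analysed (EQ-VAS or EQ-5D).
- Enter the same symptom severity scores in the hospitalisation and mortality models.
- State that the adjusted contrast is the main result and that the t-test or rank test is descriptive.
- Interpret the adjusted contrast as the 12-month difference between patients with the same starting point. Add a sensitivity model without baseline EQ-VAS, because baseline scores may already reflect earlier recognition or treatment.

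The cost is analysis-plan wording and one extra model. No new data or patients are needed.
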